### Analysis

#### Sample size calculations

Power calculations were based on the primary outcome variable, the NRS score, and a pooled mean (standard deviation) baseline score across groups of 3.250 (2.975) from Davies et al., 1998 [15] (with correction, 1999). Thomson and Williams’ 2000 [31] article on testing the xerostomia inventory was used to estimate patients’ ICC (intra class correlation). In their table IV, Thomson and Williams give a correlation between standard-question responses that range from 0.20 to 0.76, so we assumed a value of 0.3 (approximately the median). From Bland 2000 [32] [page 204], recognising that r ≈ ICC = *s*_
*b*
_^2^/ (*s*_
*b*
_^2^ + *s*_
*w*
_^2^) where *s*_
*b*
_^2^ is the between subject variance and *s*_
*w*
_^2^ is the within subject variance, we can thus determine that *s*_
*w*
_^2^ ≈ 4.752. Of the 70 palliative care patients randomized by Davies et al. [15], 36 (51%) completed phase I (14 days in length) and 26 (37%) completed phase II (21 days in length after phase I completion). Based on this attrition rate, but recognizing the shorter duration of our study, we expect that approximately 60% of our patients will complete cycle I, 50% will complete cycle II, and 45% will complete cycle III.

If we assume no period effect or treatment × time interaction, then simulations of size N = 10,000 in Stata (Statacorp, College Station, TX) programmed to model the repeated measures design, attrition rates, and *s*_
*b*
_^2^ and *s*_
*w*
_^2^ variances above, then n = 70 patients need to be recruited to detect a 2 cm change in NRS scores between treatments with 80% power at the 5% level of significance. With n = 70, we expect 31 patients will complete all 3 cycles, 4 will complete cycles I and II, 7 will complete cycle I, and 28 will fail to complete any cycles. In contrast, a conventional RCT with similar attrition would require 120 patients.

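### The within-patient variance of 4.752 does not follow from SD 2.975 and ICC 0.3, and n = 70 at 80% power does not follow from 4.752

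*Protocol article*

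**What the plan says.** All the inputs are in one section of the protocol article, Sample size calculations.

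- The spread comes from an earlier trial: "a pooled mean (standard deviation) baseline score across groups of 3.250 (2.975").
- The ICC comes from a xerostomia-inventory paper: "a correlation between standard-question responses that range from 0.20 to 0.76, so we assumed a value of 0.3 (approximately the median").
- The ICC is defined as s_b²/(s_b² + s_w²), between-patient variance over the sum of between- and within-patient variance. From this the section concludes that s_w² is about 4.752. It gives no value for s_b².
- Attrition: "approximately 60% of our patients will complete cycle I, 50% will complete cycle II, and 45% will complete cycle III".
- Model: "If we assume no period effect or treatment × time interaction, then simulations of size N = 10,000 in Stata", run with the attrition rates and the two variances.
- Result: "n = 70 patients need to be recruited to detect a 2 cm change in NRS scores between treatments with 80% power at the 5% level".
- At that size, "we expect 31 patients will complete all 3 cycles, 4 will complete cycles I and II, 7 will complete cycle I, and 28 will fail". The last group of 28 would supply no finished cycle. A conventional RCT with similar attrition is put at 120 patients.

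**The concern.** The section presents 4.752 as a consequence of the SD and the ICC, but the stated identity does not return it from those two numbers. Every patient receives both treatments in each cycle, so s_b² cancels from the treatment difference. With no period effect or interaction in the model, s_w² sets the precision of the comparison. It is therefore the input that the sample size depends on most, and it conflicts with the two figures it is said to come from.

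The output raises a second problem. A variance of 4.752 is small for a 2-point difference over roughly a hundred cycles, so power of only 80% looks too low. What is at stake is whether a reader can tell which variance split produced n = 70, and so what power the trial has.

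**Working it through.** **1. Variance from the stated inputs.** SD² = 2.975² = 8.851; ICC = 0.3.

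- *2.975 as total SD:* s_w² = (1 − 0.3) × 8.851 = 6.195 and s_b² = 2.655. The printed 4.752 would imply ICC = 1 − 4.752/8.851 = 0.463. Keeping both 0.3 and 4.752 would need a total SD of √(4.752/0.7) = 2.61.
- *2.975 as between-patient SD:* s_w² = 8.851 × 0.7/0.3 = 20.65. The printed 4.752 would imply ICC = 8.851/(8.851 + 4.752) = 0.651.

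Neither reading gives 4.752.

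**2. Power at n = 70.** The expected completers are 31 with three cycles, 4 with two and 7 with one: 42 patients and 93 + 8 + 7 = 108 cycles. Assumptions: one value per period, two-sided 5%, no treatment-by-patient variance. A cycle difference then has variance 2s_w². Two simple estimators bracket the plausible analyses:

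- cycles pooled: SE = √(2s_w²/108)
- mean of patient means: SE = √(2s_w² × (31/3 + 4/2 + 7))/42 = √(2s_w² × 19.33)/42

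Power = Φ(2/SE − 1.96).

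| s_w² | Origin | SE, pooled | Power, pooled | SE, patient means | Power, patient means |
|---|---|---|---|---|---|
| 4.752 | as printed | 0.297 | >99.99% | 0.323 | >99.99% |
| 6.195 | 0.3, total SD | 0.339 | >99.99% | 0.369 | 99.97% |
| 20.65 | 0.3, between-patient SD | 0.618 | 89.9% | 0.673 | 84.4% |
| 22.56 | 4.75² | 0.646 | 87.2% | 0.703 | 81.2% |

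A 10,000-run simulation of patient means with a t test gave 100%, 99.9%, 82.8% and 79.8% for the four rows.

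Solving instead for the number recruited at 80% power, with the stated attrition, gives 13 to 15 for 4.752, 16 to 19 for 6.195, 53 to 62 for 20.65 and 58 to 68 for 22.56. Only the last comes close to 70.

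**3. What 22.56 would require.** ICC = 8.851/(8.851 + 22.56) = 0.28, with 2.975 as the between-patient SD.

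**4. Which role 2.975 plays in the RCT figure.** Taking 2.975 as the full SD, the normal formula gives 2 × (1.96 + 0.84)² × 8.851/4 = 34.7, so 35 per arm and 70/0.6 = 117 after 40% attrition. The t-based formula gives 35.7, so 36 per arm and 72/0.6 = 120, the stated figure. The RCT comparison thus fits 2.975 as the full SD.

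**5. Range over the quoted correlations, 0.20 to 0.76.** With 2.975 as total SD, s_w² runs from 0.80 × 8.851 = 7.08 to 0.24 × 8.851 = 2.12, and power is at least 99.9% throughout. With 2.975 as between-patient SD, s_w² runs from 8.851 × 0.80/0.20 = 35.40 to 8.851 × 0.24/0.76 = 2.79. At 35.40 the SEs are 0.810 (pooled) and 0.881 (patient means), so power is Φ(0.51) = 70% and Φ(0.31) = 62%.

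**The case against.** The best defence is that 4.752 is 4.75² with a lost superscript. That value nearly reproduces n = 70, and its ICC of 0.28 would round to 0.3. This is a serious possibility, and it may be what was simulated. Two things count against treating it as settled. Other squared terms in the same sentence kept their superscripts. And an ICC of 0.3 as stated gives 20.65, not 22.56. Even if the reading is right, it uses 2.975 as the between-patient SD while the 120-patient figure fits it as the full SD, so the section still needs correcting.

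A second defence is that the simulation may have been richer than these formulas. Independent values on days 2 and 3 would raise power and widen the gap. Treatment-by-patient variance would lower power, and the design does expect individual variation in response. But the section names only s_b² and s_w² as the variances modelled. For 4.752 to give 80% power by patient means, the variance of the estimate would have to be (2/2.80)² = 0.51. The within-patient part supplies 2 × 4.752 × 19.33/42² = 0.104. The remainder, about 0.406 × 42 = 17, is a treatment-by-patient SD of about 4.1 points on a 0–10 scale, which nothing in the section suggests.

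A third defence is that nothing follows for the trial, since power is ample under the total-SD reading. That stands as far as it goes, and it limits the point to an irreproducible input and output.

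Three stronger readings are tempting and are not supported. A reader might infer that the simulation was run on 4.752 with an ICC of 0.46, so that the standard error is 14% too small (√(6.195/4.752) = 1.14). A run on 4.752 would not have returned 70 patients at 80% power under the model described. A reader might infer that the trial is too small. That needs the between-patient reading together with a correlation near the bottom of the quoted range, and the document adopts neither. A reader might infer that it is several times too large. That takes 4.752 or 6.195 as the true variance, which the stated n contradicts.

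**Conclusion.** The point holds on two counts. First, the printed within-patient variance does not follow from the stated SD and ICC: it should be 6.195 or 20.65, depending on the role of 2.975. This is arithmetic on printed figures and needs no further assumption. Second, the stated 80% power at n = 70 does not follow from the printed variance: power is about 99.97% or more with 4.752 or 6.195. It is about 81% by patient means only under the 4.75² reading. These power figures assume the stated completers, one value per period, a two-sided 5% test and no treatment-by-patient variance.

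The document cannot settle which variance was simulated. It therefore supports no claim about the direction or size of an error in n, and does not show that the trial is underpowered.

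**What to change.** In Sample size calculations:

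1. State the s_b², s_w² and ICC actually used in the simulation, and say whether 2.975 is the total or the between-patient SD.
2. Correct whichever figure is inconsistent. If 4.75² was meant, print it as such, give the ICC behind it, and reconcile the role of 2.975 with the 120-patient RCT figure.
3. Rerun the simulation on the stated values, and restate the power or the detectable difference at n = 70.
4. Report the same result over the quoted correlations, 0.20 to 0.76. The total-SD and between-patient readings give very different answers at the low end.

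The cost is a text correction and one rerun of an existing program. No change to design, analysis or enrolment is asked for.

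### The stated 80% power for a 2-point difference at n = 70 does not follow from the protocol's own inputs, which give power above 99%

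*Protocol article*

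**What the plan says.** All of this is in the protocol article, under Sample size calculations.

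- **Target:** the section concludes that "n = 70 patients need to be recruited to detect a 2 cm change in NRS scores between treatments with 80% power", at the 5% level.
- **Variance inputs:** a "pooled mean (standard deviation) baseline score across groups of 3.250 (2.975"), taken from an earlier palliative care trial. For the intra-class correlation, the authors cite a range of 0.20 to 0.76, "so we assumed a value of 0.3 (approximately the median"). From these they derive a within-subject variance of about 4.752.
- **Attrition:** about 60%, 50% and 45% of patients are expected to complete cycles I, II and III. At n = 70, "we expect 31 patients will complete all 3 cycles, 4 will complete cycles I and II, 7 will complete cycle I", and 28 complete none.
- **Model:** the simulation is described as using the repeated-measures design, the attrition rates and the between- and within-subject variances. Period effects and treatment-by-time interaction are assumed absent. No variance for the treatment effect between patients is named.
- **Comparator:** "a conventional RCT with similar attrition would require 120 patients".

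The section on aggregated n-of-1 trial design confirms that each cycle is a within-patient pair of active and placebo periods.

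**The concern.** Each cycle compares active drug with placebo in the same patient, so the between-patient variance cancels from the treatment difference. What remains is a within-patient SD of about 2.2 points (the square root of 4.752), averaged over more than a hundred pairs. A 2-point effect should then be detected almost with certainty, and 80% looks far too low.

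This calculation is the only justification given for recruiting 70 patients with advanced cancer. It also supplies the one numerical comparison in the article for the claim that n-of-1 trials need far fewer patients than a conventional RCT. A reader who wants to know what effect the trial can detect, or who reuses the 70 v 120 contrast, would be working from a figure that cannot be reproduced.

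**Working it through.** **Inputs from the sample size section.** Patients by completed cycles: 31 with three, 4 with two, 7 with one. Within-subject variance s_w² = 4.752. Difference 2 points, 5% level (taken as two-sided; the article does not say). One value per period is assumed.

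**Step 1: amount of data.** Cycles: 31×3 + 4×2 + 7×1 = 93 + 8 + 7 = 108. Patients: 31 + 4 + 7 = 42, which is 60% of 70.

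**Step 2: variance of one cycle difference.** 2 × s_w² = 2 × 4.752 = 9.504.

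**Step 3: standard error (SE).**
- All cycles pooled: √(9.504/108) = 0.297.
- Unweighted patient means: √[9.504 × (31/3 + 4/2 + 7/1)]/42 = √(9.504 × 19.33)/42 = 0.323.

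**Step 4: power for 2 points.** 2/0.297 = 6.7 SEs, or 2/0.323 = 6.2 SEs. Power from the noncentral t exceeds 99.9% either way. Simulation at n = 70 with random attrition gave 100% (pooled) and 99.95% (patient means). The stated 80% is not reproduced.

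**Step 5: consistency of the variance.** Total variance is 2.975² = 8.851. With ICC 0.3, s_w² = 0.7 × 8.851 = 6.195, not 4.752. Conversely, 4.752 implies ICC = 1 − 4.752/8.851 = 0.46.

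**Step 6: results over the plausible readings at n = 70.**

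| s_w² | Analysis | SE | Power for 2 points | Difference with 80% power |
|---|---|---|---|---|
| 4.752 | pooled cycles | 0.297 | >99.9% | 0.84–0.85 |
| 4.752 | patient means | 0.323 | >99.9% | 0.93 |
| 6.195 | pooled cycles | 0.339 | >99.9% | 0.96–0.97 |
| 6.195 | patient means | 0.369 | >99.9% | 1.06 |
| 8.851 (all variance within patient) | pooled cycles; patient means | 0.405; 0.440 | 99.8%; 99.3% | 1.14; 1.26 |
| 4.752; 6.195 | cycle I only, 42 patients | 0.476; 0.543 | 98%; 95% | 1.36; 1.56 |

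The small ranges for pooled cycles come from using 107 or 41 degrees of freedom.

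**Step 7: recruits needed for 80% power at 2 points**, by simulation with random attrition. With s_w² = 4.752: about 14 to 16 (pooled) or 18 to 20 (patient means). With 6.195: about 18 (pooled) or just under 24 (patient means). Overall, about 14 to 24.

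**Step 8: treatment effects that differ between patients.** This component is not among the stated inputs, so its SD, τ, is an assumption. With patient means, SE = √(42τ² + 2 s_w² × 19.33)/42.
- τ = 2, s_w² = 4.752: √(168 + 183.7)/42 = 0.447; power 99%; 80% at 1.28 points.
- τ = 2, s_w² = 6.195: √(168 + 239.6)/42 = 0.481; power 98%; 80% at 1.38 points.
- To bring power down to 80%, τ would have to be 4.0 (4.752) or 3.8 (6.195).

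**Step 9: the RCT comparator.** Two groups, SD 2.975, 2 points: 2 × 8.851 × 7.849/4 = 34.7, so 35 per arm (36 with the t-test). With 60% retention, 70/0.6 = 117 or 72/0.6 = 120. The stated 120 reproduces.

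**The case against.** The strongest reply is that the simulation may have held more than the article lists. Variation in individual response is one of the article's own conditions for an n-of-1 trial, and the planned hierarchical model estimates individual effects. A treatment-effect variance in the simulation would lower power. That is fair as far as it goes, but it would take an SD near 4 points on a 0–10 scale to reach 80%, and no such component is mentioned.

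Other routes do land near 80%. A parallel-group test with 35 per arm and no attrition gives 80.3% with 70 patients. Reading 4.752 as an SD gives 79.3% with patient means, and reading 2.975 as the between-patient SD (s_w² = 20.65) gives 83%. Any of these might explain the slip, but none is what the article states, and the last two contradict its variance figures.

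Three objections limit the point, and they stand:

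- **No single detectable difference is fixed by the document.** It depends on the variance, on the weighting, and on whether s_w² refers to a day or a period. Days 2 and 3 are both analysed. If the variance is per day with independent errors (an assumption), the range falls to about 0.59–0.75.
- **A reader might infer that the whole 70 v 120 comparison is wrong.** It is not: 120 reproduces, and a corrected 70 would favour the n-of-1 design more strongly.
- **A reader might infer that a positive result will be passed off as a 2-point benefit.** An observed difference of about 0.6 (1.96 × 0.297 = 0.58) would exclude zero. But the Data analysis section reports the posterior mean with a 95% credible region, and the article sets 2 points as the clinically important change. The documents do not support that fear.

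**Conclusion.** The point holds: the power statement is wrong as written. On the stated inputs, 70 recruits give more than 99.9% power for 2 points, and power stays above 99% even if the whole variance is treated as within-patient. Given one value per period and no treatment-effect variation, the difference detectable with 80% power is about 0.85 to 1.06 points. With an assumed treatment-effect SD of 2, it is about 1.3 to 1.4 points. The conflict between 4.752 and the stated SD and ICC is a second defect in the same paragraph, but it does not account for the gap.

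It would be tempting to conclude that the trial is badly sized or its validity impaired. The documents do not support that. The error is in the safe direction: the trial has more patients than its stated target needs, and the design, primary analysis and error rate are unaffected. This is a justification that cannot be reproduced and should be corrected, not a reason to change the trial.

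**What to change.** Keep n = 70 and correct the text:

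1. Reconcile the within-subject variance with the SD of 2.975 and the ICC of 0.3, or state the ICC actually used.
2. Rerun the simulation with the model and every variance component stated. Include any treatment-effect variance, and say whether s_w² is per day or per period and whether the test is two-sided.
3. Report what that run gives for two quantities at n = 70: power for 2 points, and the difference detectable with 80% power. Do not copy the ranges above, which depend on the assumptions shown.
4. Correct the 70 side of the 70 v 120 comparison so that both sides rest on the same inputs; the 120 can stay.

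The cost is one rerun of an existing simulation and a revised paragraph. No extra patients are needed.

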#### Data analysis

Data preparation and descriptive reporting will follow that recommended by the CONSORT statement [25].

For each cycle, data from day 1 will be discarded to allow for a wash-out period, and data from days 2 and 3 data will be analysed. All patients with at least one completed treatment cycle will be included in analyses. An effect size will then be calculated between active medication cycles and placebo, thus providing a population measure of effect commensurate with an RCT.

Both individual and population treatment differences will be estimated using hierarchical Bayesian methods and employing noninformative priors using the methods described in Zucker et al. [33], and Schluter and Ware [34]. The likelihood distributions for each model will be assessed for violations and data transformations undertaken, where necessary. Conventional burn-in periods, model convergence and stability diagnostics, and residual checks will be employed [35]. WinBUGS [35] will be used for the Bayesian analysis.

To describe participants’ overall response, three types of Bayesian results will be presented: (i) the mean of the posterior distribution of the mean difference between placebo and stimulant scores, which gives the best estimate of the overall effect size difference between treatments; (ii) the associated 95% credible region, which give intervals of uncertainty (in this case the 2.5 and 97.5 percentile) of the posterior distributions used in (i); and (iii) the posterior probability of the mean difference that stimulant scores were better than placebo scores, which describes the likelihood that the patients will favour the active treatment in future cycles [34]. A patient will be defined to be a ‘responder’ when these estimated values exceed predefined threshold values [34].

Important confounding variables, such as anti-cholinergic load and cause of xerostomia (eg prior radiotherapy), will in included in adjusted analyses and report treatment effects (or success differences) over the various variable stratifications and combinations, following the method advocated by Zucker and colleagues [33].

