### Aggregated n-of-1 trial design

This will be an n-of-1 trial with 3 pairs (cycles) of treatment periods comparing active drug to placebo. As pilocarpine has a short half life (0.76 hours for 5 mg tabs), the clinical effect is rapidly evident. Therefore, an appropriate duration of each treatment period is 3 days (thus each treatment pair (or cycle) is 6 days), making a total of 18 days for patients who complete the full trial. The order of drugs in each cycle will be determined by random allocation, blinded to both clinician and patient. Patients who do not complete the full trial will still contribute completed cycles to the final analysis. To produce a population estimate of a treatment effect, the results of all patient cycles will be aggregated [18].

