### Trial medication

a) *Active pilocarpine*

Active pilocarpine hydrochloride 4% (40 mg/ml) in citrus solution; 3 drops orally, three times per day (6 mg per dose) with meals, or identical placebo 3 drops three times daily, will be provided in identical opaque bottles and delivered with a mouth dropper. The dose was chosen based on previous studies [15] and a previous report that pilocarpine (15-30 mg/day) improves symptoms in about 50% of patients, compared 25% of patients taking placebo [20]. Placebo and treatment will have identical taste and color, the strong taste of pilocarpine being masked by citrus. The patients will administer the drops themselves unless assistance is required by a clinical nurse.

Trial packs of bottles will be pre-packed by a pharmacy to allow commencement of the trial as soon as the patient is recruited. The drops are stable for one month. The bottles will be labeled with a randomisation number to keep allocation blinded. Single cycle, 6 day packs will be prepared, with random allocation of the order of the medicines determined by computer, individually numbered and allocated to patients consecutively. The Discipline of General Practice at UQ will run the trial centrally and provide randomised medications and diaries by post to the trial sites for dispensing to patients.

b) *Concomitant therapy*

Regular medications will be continued as required for other conditions. Patients who are prescribed new medicines or increased doses of prior medicines that are likely to affect their xerostomia during a cycle will be withdrawn temporarily from the trial, and data from that cycle discarded. The trial can recommence when effects of the change have been stabilised for at least 1 week.

*Compliance* with the study will be measured by bottle weights and completion rates of the diaries at 18 days and will be encouraged by regular telephone calls from the project officer.

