#### Secondary outcomes

1. Mean xerostomia inventory score [23];

2. Oral health related quality of life;

3. Adverse events (according to NCI Common Terminology for Adverse Events [24]);

4. Dysphagia (difficulty swallowing);

5. Dysgeusia (distortion of taste);

6. Global impression of change.

The trial will be reported according to the Consort statement [25], and analysis will be on an intention-to-treat basis.

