(i) Oral health related quality of life will be measured by Oral Health Impact Profile (OHIP) [29], a short 14 item questionnaire that has been validated in a population with xerostomia, although not in cancer or PC.

(a) *Patient Global Impression of Change (PGIC)*:

Is a standardised, validated questionnaire that addresses change in activity limitation, emotions, symptoms and overall quality of life [30].

2. *Timing and content of assessments*

3. *Individual patient reports*

At the end of the trial, the order of medications will be unmasked, and compared with the patient’s observations. Repeated results in the same direction favouring the treatment will be reported in terms of a probability that the observed result is true. The clinical importance of the result will be described by comparing it to a predetermined clinically important change. A clinically significant response to pilocarpine or placebo will be defined as a ≥2 point improvement in xerostomia NRS score compared to baseline, in view of previous work, where a 20% (2 cm) improvement or more against the baseline NRS score was considered to be a positive improvement [21,22]. A report on the patient’s response to pilocarpine will be forwarded to the patient’s doctor so a decision on further treatment can be made.

Palliative care clinicians who recruit participants will most likely also receive the post-treatment report. This potentially may unblind the clinician during the course of the trial in relation to the possible effectiveness of pilocarpine, and particular characteristics of responders. Ideally the clinician recruiting to the study will be a different to the one receiving the results and treating the patient. Collecting data from patients independent of clinicians minimises observer bias.

4. *Withdrawals*

Patients who discontinue the study for whatever reason will be able to resume if their condition can be re-stabilised for at least 1 week. Patients who cannot resume the trial will have their completed cycle results added to the trial dataset for later calculation of the population effect of pilocarpine. If a patient’s withdrawal from the study could be attributed to the intervention, their data will contribute to the analysis under intention to treat principles.

**Table 1 T1:** Schedule of assessments

**Measure**	**Baseline**	**Daily**	**Every 3 days**	**End of 6 day cycle**	**End of trial**
Demographics	x				
Vital Signs	x				
Routine blood test	x				
AKPS	x				x^1^

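### The analysis is labelled intention-to-treat but rests on completed cycles, with an exception that contradicts that rule; up to 40% of recruited patients may fall outside it

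*Protocol article*

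**What the plan says.** All places are in the protocol article.

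- **Secondary outcomes** (closing sentence): "analysis will be on an intention-to-treat basis".
- **Data analysis**: "All patients with at least one completed treatment cycle will be included in analyses".
- **Aggregated n-of-1 trial design**: "Patients who do not complete the full trial will still contribute completed cycles to the final analysis".
- **Patient assessment, item 4 (Withdrawals)**, for permanent stoppers: "Patients who cannot resume the trial will have their completed cycle results added to the trial dataset". The next sentence adds an exception. If "withdrawal from the study could be attributed to the intervention, their data will contribute to the analysis under intention to treat principles".
- **Trial medication, b) Concomitant therapy**: patients with a new or increased medicine likely to affect xerostomia "will be withdrawn temporarily from the trial, and data from that cycle discarded". They may restart after at least one week of stability.
- **Sample size calculations**: 60%, 50% and 45% of patients are expected to complete cycles I, II and III. With 70 recruited, "28 will fail to complete any cycles".
- **Efficacy of pilocarpine in reducing xerostomia?**: in the cited review, side effects were the main reason for withdrawal, in 6 to 15% of patients on 5 mg three times a day.

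**The concern.** In a trial that randomises the order of treatments within each cycle, intention-to-treat means that every randomised patient's data are analysed by the treatment allocated to the period. A rule that counts only completed pairs conditions on something that happens after randomisation and that the drug itself can influence. Discarding a cycle because a medicine was added or increased has the same feature.

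Two things are at stake. First, two analysts who follow this text in good faith could build different primary datasets. Second, the main aim is a population estimate, which the Data analysis section likens to that of a conventional randomised trial. If those who complete a cycle differ in treatment effect from those who do not, the estimate describes the completers only, while the label tells readers otherwise.

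**Working it through.** **1. Reproduce the plan's forecast** (inputs: n = 70 and completion of 60%, 50% and 45%, from Sample size calculations).

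- Complete cycle I: 70 × 0.60 = 42
- Complete cycle II: 70 × 0.50 = 35
- Complete cycle III: 70 × 0.45 = 31.5
- All three cycles: 31.5; cycles I and II only: 35 − 31.5 = 3.5; cycle I only: 42 − 35 = 7; none: 70 − 42 = 28

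The plan states 31, 4, 7 and 28, which sum to 70. The figures agree apart from rounding.

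**2. Size of the completed-cycle set.**

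- Patients inside: 42/70 = 60%. Outside: 28/70 = 40%.
- A further 4 + 7 = 11 patients lose one or more later cycles.
- Cycles inside: 31×3 + 4×2 + 7×1 = 108 of 70×3 = 210, or 51%.

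**3. Effect of the exception.** The plan does not forecast withdrawals attributable to the intervention. Assume the cited review's 6 to 15% applies here and that all of these patients stop in cycle I:

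- 0.06 × 70 = 4.2 patients return: (28 − 4.2)/70 = 34% still outside.
- 0.15 × 70 = 10.5 patients return: (28 − 10.5)/70 = 25% still outside.

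So 40% is an upper figure. On this assumption, 25 to 34% remain outside even if the exception is applied in full.

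**4. Test the rules on one case.** A patient is allocated placebo then pilocarpine in cycle I, finishes the placebo period with day 2 and 3 scores, and stops early in the pilocarpine period.

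| Reason for stopping | Data analysis rule | Withdrawals rule |
|---|---|---|
| Side effects | Not in the set (no completed cycle) | Data contribute |
| Disease progression | Not in the set | Only completed cycles, so nothing |

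Two patients with identical diaries are treated differently according to a judgement of cause. In the first row, the two sections also disagree with each other. Nothing says how a placebo period without its active partner would enter the model.

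**5. What exclusion could do to the estimate (illustration only).** Assume a mean difference of 2 points in the 42 included patients and x in the 28 excluded. The mean over all 70 is (42×2 + 28x)/70.

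| x | All 70 |
|---|---|
| 3 | 2.4 |
| 2 | 2.0 |
| 1 | 1.6 |
| 0 | 1.2 |
| −1 | 0.8 |

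The documents give no value for x. The completed-cycle figure could be too high, right or too low.

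**6. Power.** The 28 non-completers are already allowed for in n = 70, so this point does not change the sample size.

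**The case against.** The strongest reply is that the Withdrawals exception is aimed at exactly the dropouts that matter. The Data analysis sentence says who is included without the word *only*, so the exception can be read as a supplement. Part of this stands: the plan does address treatment-related withdrawal, and it is wrong to say that all 28 patients necessarily contribute nothing. But the exception gives no method, depends on attribution, and still leaves out other stoppers. It does not make the analysis intention-to-treat.

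Other points on that side also stand:

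- The 40% comes from forecast non-completion of cycle I, based on attrition in an earlier palliative care trial. The medication-change rule drops single cycles and allows restart, and no number is forecast for it. It is not a source of the 40%.
- No reasons are given for the expected attrition. In advanced cancer much of it may be decline or death unrelated to treatment. The 6 to 15% comes from a review in radiotherapy-related dysfunction.
- Dropping a whole cycle removes its active and placebo periods together, so bias requires that dropouts differ from completers in effect. Intolerance is not lack of relief. Side effects reflect the drug's general parasympathomimetic action, so patients who stop for them may respond as well or better.

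A reader might therefore infer that the rule keeps tolerators and inflates the benefit, for example by a quarter (2.0/1.6 = 1.25). That figure rests wholly on assuming half the benefit in all excluded patients, and the documents support neither the figure nor the direction.

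Finally, withdrawal tables and missing-data sensitivity analyses are commonly left to the analysis plan. Their absence here is no finding. The contradiction in the published text is.

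**Conclusion.** The point holds as a conflict over who and what enters the primary analysis. The intention-to-treat statement is not met by the completed-cycle rule or by discarding medication-change cycles, and the attribution-based exception contradicts the Data analysis section without saying how to apply it.

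By the plan's own forecast, up to 28 of 70 recruited patients (40%) and about half of the planned cycles lie outside the completed-cycle set. The patient figure falls if the exception is used, to 25 to 34% on the borrowed withdrawal rates.

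That exclusion may depend on treatment follows from the protocol's own account of why patients stop pilocarpine. The share that does is unknown, so bias in the population estimate is possible but unquantified. The finding does not extend to a 40% loss caused by treatment, to a definite overstatement of benefit, or to any loss of power.

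**What to change.** Reconcile the four places (Concomitant therapy, Secondary outcomes, Withdrawals, Data analysis) before unblinding. This concerns the use of data only, not the clinical rules for stopping or restarting.

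1. **Primary set.** Include every randomised patient with any analysable day 2–3 NRS score, by the treatment allocated in that period. Let unfinished cycles enter the hierarchical model at period level. Say explicitly that the model has patient-level effects and is not built on within-pair differences alone: a lone period gives no within-patient contrast and informs the population estimate only through comparison between patients.
2. **Exception.** Delete the attribution-based clause; rule 1 makes it unnecessary.
3. **Sensitivity analysis.** Keep completed cycles only.
4. **Medication-change cycles.** Report results with these cycles excluded and, where scores were recorded, included. State in advance which is primary. This is a choice of estimand, because including them mixes in the effect of the other medicine. The article does not promise diary entries during temporary withdrawal.
5. **Alternative.** If the completed-cycle set stays primary, call it a completed-cycle (modified intention-to-treat) analysis and drop the intention-to-treat claim.

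The cost is wording and slightly more modelling, since the NRS is already scheduled daily. Patients with no score after day 1 remain missing under any version, and the estimate may change.
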